## Follow-up of AEs and SAEs

All AEs and SAEs documented at a previous visit/contact and are designated as ongoing, will be reviewed at subsequent visits/contacts.

All AEs and SAEs will be followed until resolution, until the condition stabilises, until the event is otherwise explained, or until the Participant is lost to follow-up. Once resolved, the appropriate AE/SAE CRF page(s) will be updated.

## 8.7 Risk Management Process

Table 2 below details the Risk Identification, Evaluation and Management plan for this study.

It will ensure that risk and uncertainly are appropriately managed for the duration of the study. The risk management process is in accordance with the NHMRC National Statement on Ethical Conduct in Research Involving Humans (2007).

**Table 2: Risk Analysis Matrix**

| **Consequence** | **Response To Risk** |
| --- | --- |
| | **Likelihood** | **Negligible** | **Minor** | **Moderate** | **Major** | **Extreme** | | --- | --- | --- | --- | --- | --- | | Almost Certain |  |  |  |  |  | | Likely |  |  |  |  |  | | Possible |  |  |  |  |  | | Unlikely |  |  |  |  |  | | Rare |  |  |  |  |  | | |  | Very High | Immediate action required | | --- | --- | --- | |  | High | Urgent attention or investigation required | |  | Medium | Require specific attention | |  | Low | Manage through routine procedures | |

**Risk** Identification, Evaluation and Management Plan

|  | Risk | Description | Possible Effects | | | Risk Management strategies |
| --- | --- | --- | --- | --- | --- | --- |
| Likelihood | Consequence | Rating |
| 1. | Psychological discomfort during assessments | Participants may experience psychological discomfort when answering questions in the clinical interview and cognitive assessments. | Possible | Minor-moderate | Medium | The PICF clearly states the potential risk of discomfort.  Recruitment of experienced mental health clinicians who will be able to minimise and manage discomfort.  Participants will be clinically assessed at baseline, 3 weeks and at 8 weeks. Participants are given the opportunity to discuss any concerns/discomforts re previous appointment.  Clinicians will direct and assist participants to gain support if required. |
| 2. | Inconvenience of participating in the trial | Participants may be inconvenienced by time taken to participate in the trial. | Possible | Negligible | Low | The PICF clearly states the battery of clinical assessments and physical interventions to be completed and the approximate time and frequency for clinical assessment and physical intervention visits.  Participants will be given as many breaks as necessary throughout the clinical assessment visit.  Participants will be provided with either baseline and post intervention gift cards, or Garmin Vivofit wearable device for their time involved in the trial.  Participants will be reminded that the trial is voluntary and they can withdraw at any time. |
| 3. | History of self-harm/suicidal ideation | Participant expresses suicidal ideation. | Possible | Moderate-severe | High | Recruitment of experienced mental health clinicians who are trained in conducting risk assessment and managing high risk situations.  Research staff will have access to a clinically trained senior staff and Chief Investigator who will assist research staff to conduct risk assessment and implement risk management plan if required i.e. notifying treating team and assisting in the participant accessing appropriate support (e.g. emergency services)  Research staff will be given support and feedback on risk assessments and their management to improve skills throughout the project.  Residents of CCU’s must be low imminent risk of suicide and aggression to be able to reside in residential facilities and are screened for risk by the admitting consultant psychiatrist before admission. |
| 4. | Physical discomfort | Participant experiences an injury during the intervention | Possible | Minor – moderate | Medium | AEP will be conducting the intervention and will monitor participants for any type of injury or physical discomfort and treat and report according to the facilities policy and procedures.  The interventions will be tailored to take into consideration the participant’s level of fitness. |

# Participant Completion and Discontinuation

## Participant Completion

Participants are considered to have completed the study if they complete 8 weeks of intervention. The number of supervised exercise sessions attended by participants in each condition (RT and MIIT group) as a proportion of total available sessions (3 sessions per week for 8 weeks - 24); feasibility will be defined by attendance at greater than 60% of sessions (15 sessions).

Participants will be asked to complete post measures even if they are withdrawn from the study intervention, where possible.

## Participant Withdrawal by the Investigator

Worsening of mental state such that the patient is admitted to hospital or their ability to provide ongoing informed consent is compromised or physical injury preventing the participant from continuing in the clinical trial.

# Case Report Form (CRF)

A Case Report Form (CRF) will be completed for each study participant summarising all clinical screening and study data that will be used by the research team for analysis. In the CRF, participants will only be identified by their participant number in order to retain participant confidentiality.

The completed Case report Forms (CRF’s) will be retained by the Investigators for a period of at least 15 years or the maximum time frame as determined by local regulations, whichever is the longest.

# Data Analysis and Statistical Considerations

## Hypotheses

We hypothesise that stand alone RT will be feasible and acceptable to people with psychotic disorders accessing residential rehabilitation.

## Endpoints

### Primary

Stand-alone RT will be feasible and acceptable compared to control, aerobic interval training (AIT) based on recruitment, retention and participation.

### Secondary

Comparison of stand-alone RT with control, aerobic interval training(AIT) with respect to mental (functioning, mental health symptoms) and physical health outcomes

Allocation to exercise condition the participant expresses preference for prior to randomisation will result in increased adherence.

Comparison of psychological responses to a single session of exercise (week 3 and 8) between exercise conditions, RT and MIIT will be identified

## Sample Size and Power

This study will be conducted as an exploratory RCT with feasibility as the primary outcome. Based on recruiting an adequate sample to assess the feasibility of the study with the resources available (63) we aim to recruit 50 participants assuming approximately 25 participants will be assigned to each intervention arm, based on previous exercise research within this setting – we anticipate 20% drop outs per exercise condition (49).

## Statistical Analysis

Data analyses will be conducted using SPSS Statistics 24, (SPSS Inc, Chicago, Illinois) for the primary outcomes. Continuous variables were summarized using means and standard deviations (SD) (or median and interquartile range for non-parametric data). All variables will be tested for normality using the Shapiro-wilks test, and visual inspection of Q-Q plots. Baseline demographic and clinical variables, participation and AE rates and mean aggregate acceptability scores will be compared between the two exercise groups using independent t-tests or Mann-Whitney U for non-parametric data. Chi square analysis for categorical data will be used to detect any baseline differences between the two exercise groups and for comparison of acceptability categories (strongly agree/agree versus other) per questionnaire item between the groups.

Baseline demographic and clinical variables will be compared between the 2 exercise groups using independent t tests (or Mann Whitney U tests if data non parametric) for continuous data and Chi2 square analysis for categorical data to detect any baseline differences between the 2 exercise groups. Baseline characteristics of those who complete >50% of the program will be compared to those who withdraw to identify characteristics of those who drop out.

To analyse the impact of the proposed exercise intervention on secondary outcomes, analyses will be performed on an intention-to-treat basis. Change from baseline in secondary outcomes at week 8 will be calculated as least squares (LS) means using a Linear Mixed Effects Model (LMM). Treatment group (RT or AIT) and time will be used as factors, with covariates established in previous similar research (age, gender, participation, and antipsychotic medication use),(García-Garcés et al., 2021b). Where group/time differences were detected, posthoc (Bonferroni) analyses will be carried out separately for the intervention and control group, with Cohen’s d estimate of effect sizes provided. LMM was performed using R (software version 4.04, 2024). All the statistical tests were two-tailed with the critical P value for significance set at?<?0.05.

For the RT group only, 12 RM strength will be assessed for normality and compared pre and post the intervention using paired samples t test.

To examine the association between exercise preference prior to randomisation with participation, a one-way ANOVA compared exercise participation rates between three groups; (i) those who randomly received their exercise preference, (ii) those who did not, (iii) those who expressed no exercise intervention preference.

The three feeling state domains from the SEES would be assessed using a group (RT, MIIT), time (pre/post) ANOVA with repeated measures. The effect size of the differences between values will be interpreted using Cohen’s *d* statistic ([Cohen, 1988](https://journals-humankinetics-com.ezproxy.library.uq.edu.au/view/journals/japa/27/3/article-p325.xml" \l "r8)). An effect size of <0.2 reflects a negligible difference; ≥0.2 to ≤0.5, a small difference; ≥0.5 to ≤0.8, a moderate difference; and ≥0.8, a large difference.

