## Primary Objectives

To assess the feasibility and acceptability of stand-alone RT compared to control, aerobic interval training(AIT) based on recruitment, retention and participation.

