11. Strength – the 12RM will be measured pre and post the intervention in large muscle groups – squat and chest press, in the RT group only (due to the complexity of the testing).

Following *completion of the trial, acceptability* will be assessed:

Participants will be asked to complete a short self-report questionnaire regarding their exercise experiences at the end of the 8-week intervention. Responses will be reported on a 5 point Likert scale, with answers from Strongly disagree, disagree, neutral, agree and strongly agree.

For those willing to participate, acceptability will also be assessed via qualitative interviews. Participants from the intervention condition (Resistance Training, RT) will be invited to engage in an individual 20-minute semi-structured interview with a researcher not involved in the delivery of the intervention. The interview will cover topics including likes, dislikes, effectiveness and recommendations for future iterations. For those participants who consent Interviews will be audio-recorded on a dictaphone and uploaded to a password protected Queensland health computer. They will be de-identified and sent to a professional transcription company to be transcribed into written content, coded as interviewer and interviewee. Data will be analysed using thematic analysis to determine key themes identified by participants (6).

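### The per-item acceptability comparisons cut each 5-point item to two categories, which usually wastes information with about 20 respondents per arm; the aggregate score and the primary feasibility criteria are not affected

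*Protocol*

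**What the plan says.** Section 6 (Study Assessments and Procedures) has participants complete a short acceptability questionnaire after the 8-week program: "Responses will be reported on a 5 point Likert scale, with answers from Strongly disagree, disagree, neutral, agree and strongly agree".

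Section 11.4 (Statistical Analysis) plans two comparisons of these data between RT and AIT:

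- For the overall score, "mean aggregate acceptability scores will be compared between the two exercise groups using independent t-tests or Mann-Whitney U for non-parametric data".
- For the single items, chi-square is named for "comparison of acceptability categories (strongly agree/agree versus other) per questionnaire item between the groups".

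The same section adds: "All the statistical tests were two-tailed with the critical P value for significance set at" 0.05.

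On numbers, section 11.3 says "we aim to recruit 50 participants assuming approximately 25 participants will be assigned to each intervention arm", and "we anticipate 20% drop outs per exercise condition".

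Section 2.1 states the primary objective as "To assess the feasibility and acceptability of stand-alone RT compared to control, aerobic interval training(AIT"). The sentence then rests that assessment on recruitment, retention and participation. The primary endpoint in section 11.2.1 has the same basis, and the feasibility criteria in section 3 set thresholds for those three measures only.

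**The concern.** An ordered 5-point response is reduced to a yes/no before the arms are compared, and the protocol gives no reason for this. The cut loses most when most people agree, because the remaining information on which program is liked more then lies largely between *agree* and *strongly agree*, which the cut merges. In the extreme case, if all 20 RT respondents strongly agreed and all 20 AIT respondents merely agreed, the dichotomised table would show no difference.

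A high level of agreement is a realistic prospect. The Introduction reports high overall acceptability of an earlier program in residential rehabilitation, with the resistance elements preferred.

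At stake is the item-by-item picture of which features of RT are received better or worse than those of AIT. The aggregate score cannot supply that, and it is useful for refining the program.

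**Working it through.** **Figures in the plan.** There is no power calculation for acceptability to reproduce; the sample size is justified by feasibility and resources. Respondents at week 8: 25 × (1 − 0.20) = 20 per arm.

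**Sparse cells (no effect size needed).** With equal arms of *n*, the expected *other* count per arm is *n* × (1 − pooled agreement).

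- *n* = 20: 20 × 0.25 = 5, so the count is below 5 once pooled agreement exceeds 75%. At 85% it is 20 × 0.15 = 3.
- *n* = 25 (no drop-out): 25 × 0.20 = 5, so the limit is 80%.

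If all 20 in one arm agree, two-sided p-values by the number agreeing in the other arm are:

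| Other arm | Pearson chi-square, uncorrected | Fisher's exact |
|---|---|---|
| 17/20 | 0.07 | 0.23 |
| 16/20 | 0.035 | 0.11 |
| 15/20 | 0.017 | 0.047 |

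**Power (assumed inputs).** The protocol gives neither item distributions nor effects, so the following are assumptions. Lower-arm probabilities, from *strongly disagree* to *strongly agree*:

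- 50% agreement: .10, .15, .25, .30, .20
- 60%: .08, .12, .20, .35, .25
- 75%: .04, .06, .15, .45, .30
- 85%: .02, .04, .09, .45, .40
- 90%: .02, .03, .05, .40, .50

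The other arm is shifted by a common odds ratio at every cut-point: odds(Y > k) in the other arm = OR × odds(Y > k) in the lower arm. Each scenario was simulated at least 20,000 times with 20 per arm and two-sided 0.05. Entries are power for tie-corrected Mann-Whitney U on five categories / uncorrected chi-square on the cut:

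| Agreement, lower arm | OR 2 | OR 3 | OR 4 |
|---|---|---|---|
| 50% | 22% / 18% | 46% / 37% | 65% / 53% |
| 60% | 21% / 18% | 45% / 34% | 63% / 47% |
| 75% | 20% / 13% | 43% / 24% | 61% / 32% |
| 85% | 20% / 9% | 40% / 14% | 57% / 18% |
| 90% | 18% / 5% | 38% / 7% | 53% / 8% |

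The smallest loss is about 4 points (3.5 before rounding, at 60% and OR 2; about 4 also at 50% and OR 2). The largest is 53 − 8 = 45 points (90%, OR 4). With 25 per arm, 75% agreement and OR 3, the figures are 52% / 30%. Under no difference, Mann-Whitney rejected in about 5% of runs, so its advantage is not bought with extra type I error.

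**Where the sign reverses.** Proportional odds moves responses along the whole scale, which suits a rank test. Suppose instead that the difference is only a move from *neutral* to *agree*: .05, .10, .35, .25, .25 against .05, .10, .05, .55, .25, that is 50% against 80% agreement. At 20 per arm, chi-square on the cut then has about 53% power and Mann-Whitney about 18%.

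**The case against.** The strongest reply has five parts.

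1. **The full scale is already used.** Section 11.4 compares the aggregate score uncut. A reader might infer that the trial's whole RT versus AIT acceptability comparison loses power, or that a report of no difference in acceptability would be a product of the cut. The document does not support that: only the per-item tests are dichotomised. This part stands.

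2. **The primary objective does not rest on the items.** Because acceptability is named in the primary objective, a reader might infer that a primary outcome is weakened. Sections 2.1 and 11.2.1 base it on recruitment, retention and participation, and section 3 sets no acceptability threshold. This part also stands.

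3. **The cut matches the question.** The hypothesis in section 11.1 is that RT is acceptable, not that it is liked more than AIT, and the percentage agreeing speaks to that directly. This is a good reason to report the percentage. It does not justify discarding the gradation in a test whose stated purpose is to compare the arms.

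4. **The size is assumed.** The trial is exploratory with no power target, so no stated figure is falsified. A reader might take a fixed loss such as 10 to 40 points from the table, but the loss depends on the assumed distribution and effect, can be smaller or larger, and can reverse. The sample size remains the main limit: full-scale power is still only about 18% to 22% at OR 2 and 38% to 46% at OR 3.

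5. **The small-cell problem is conditional.** It depends on high agreement. Section 9.1 asks withdrawn participants for post measures where possible, so respondents may exceed 20 per arm, and the choice of an exact test may be left to the statistical analysis plan. That is fair; the absence of an exact test is not itself a fault here.

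**Conclusion.** The point holds for the per-item comparisons. The protocol fixes a method that discards gradation it has gone to the trouble of collecting, and for a general shift along the scale this costs about 4 to 45 points of power per item. That range rests on assumed proportional odds, 20 respondents per arm, two-sided 0.05, 50% to 90% agreement in the lower arm and odds ratios of 2 to 4. It is not a bound, and the advantage reverses when the difference is confined to the neutral/agree boundary. The expected-count result needs only the respondent numbers and pooled agreement above 75%.

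This is an inefficiency in a supplementary analysis of an exploratory trial, not an error in the primary outcome.

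**What to change.** In section 11.4, replace the chi-square comparison of the dichotomised items with a comparison of each item on its full 5-point scale. Either use Mann-Whitney U, which that section already names, or proportional-odds regression reporting the RT versus AIT odds ratio with a 95% confidence interval. Keep the percentage agreeing or strongly agreeing per arm as a descriptive summary; if that percentage is to be tested, use Fisher's exact test.

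The cost is one sentence, with no new data, staff or participants. There are two small drawbacks. A rank-based or odds-ratio result is harder to read than a percentage, which the retained summary largely covers. Power is also lower for a difference that sits only at the cut.

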**Feasibility Criteria**

Recruitment – percentage of participants who consent to the study as a proportion of CCU residents who are referred from the three sites. Recruitment into exercise trials for people with SMI can be highly variable, however > 50% (majority) will be considered feasible.

Retention – the proportion of participants consenting to the trial who complete follow up assessments at 8 weeks as a proportion of the total number allocated in each condition. Feasibility will be defined as > 65% based on previous research (49).

Participation – the number of supervised exercise sessions attended by participants in each condition (RT and AIT group) as a proportion of total available sessions (3 sessions per week for 8 weeks - 24); feasibility will be defined by attendance at greater than 60% of sessions (15 sessions).

Participants will be evaluated at baseline and end point week 8. Total duration of the study will be 8 weeks. All outcome raters will be blind to outcome allocation, however blinding of participants to their exercise condition will not be possible.

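### The intention-to-treat mixed model for secondary outcomes adjusts for participation, a post-randomisation variable and primary feasibility outcome, which can bias the RT versus AIT comparisons

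*Protocol*

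**What the plan says.** Protocol section 11.4 states that for secondary outcomes "analyses will be performed on an intention-to-treat basis". The estimate is described as follows: "Change from baseline in secondary outcomes at week 8 will be calculated as least squares (LS) means", from a linear mixed model. "Treatment group (RT or AIT) and time will be used as factors", and the adjustment set is "covariates established in previous similar research (age, gender, participation, and antipsychotic medication use").

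The Feasibility Criteria in section 3 define participation as "the number of supervised exercise sessions attended by participants in each condition (RT and AIT group"), out of 24 sessions, with the criterion "feasibility will be defined by attendance at greater than 60% of sessions (15 sessions"). Section 7.1.5 places randomisation after consent and baseline assessment, so no session can precede allocation.

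Participation is also an outcome. The primary endpoint in section 11.2.1 reads "Stand-alone RT will be feasible and acceptable compared to control, aerobic interval training (AIT) based on recruitment, retention and participation", and section 11.4 itself says that "participation and AE rates and mean aggregate acceptability scores will be compared between the two exercise groups". Section 4.4 records medication before randomisation, so antipsychotic use can serve as a baseline covariate, as can age and gender.

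**The concern.** The plan uses one variable both as a result of allocation and as an adjustment to the effect of allocation. Holding attendance equal does two things.

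- **It removes benefit that acts through attendance.** The protocol makes this path plausible. The Introduction reports that some people with schizophrenia may prefer resistance training and links weekly exercise volume to symptom improvement. Section 11.2.2 expects that receiving the preferred condition raises adherence.
- **It can create a difference where none exists.** Anything unmeasured that drives both attendance and outcome, such as motivation or illness severity, becomes unbalanced between arms once attendance is fixed. Section 9.2 lets worsening mental state end participation, and mental state is what BPRS and SANS measure.

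At stake are the between-arm comparisons that use this model: WHODAS, BPRS, SANS, BREQ-3, and the physical capacity and physical health measures. Section 9.1 asks withdrawn participants for post measures where possible, which supports intention to treat. Adjusting for attendance works against that.

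**Working it through.** **The plan's own figures.** 0.60 × 24 = 14.4, so 15 sessions is the first whole number above the threshold (15/24 = 62.5%; 14/24 = 58.3%). This reproduces. With 50 recruited and 20% dropout (section 11.3), 50 × 0.8 = 40, or 20 per arm. The protocol gives no effect size or SD for the secondary outcomes, so all effect inputs below are assumptions.

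**Formula when change is the response.** Adjusted difference = unadjusted difference − s × Δ. Here s is the within-arm slope of change on participation and Δ is the arm difference in mean participation. There is no systematic shift if Δ = 0 or s = 0.

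**First set of assumptions.** 20 per arm, residual SD of change 1, mean participation 60% with SD 25 points, and correlation √0.5 = 0.707 between participation and an unmeasured cause. Let b be the effect of 25 points of participation and c the effect of the unmeasured cause. Then s = b/0.25 + c × 0.707/0.25, and the unadjusted difference is direct effect + (b/0.25) × Δ. Each row is 4,000 simulated trials. Participation is truncated to 0–100%, so simulated values differ slightly from the formula.

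| Direct effect, b, c | Δ | Formula: without → with | Simulated: without → with | Rejection: without → with |
|---|---|---|---|---|
| 0.30, 0.3, 0.3 (s = 1.2 + 0.849 = 2.05) | 0 | 0.30 → 0.30 | 0.30 → 0.30 | 13% → 14% |
| same | 0.10 | 0.42 → 0.42 − 0.205 = 0.215 | 0.40 → 0.21 | 20% → 10% |
| same | 0.20 | 0.54 → 0.54 − 0.41 = 0.13 | 0.52 → 0.13 | 30% → 7% |
| 0.30, 0.3, 0 (s = 1.2) | 0.20 | 0.54 → 0.54 − 0.24 = 0.30 | 0.52 → 0.30 | 33% → 13% |
| 0, 0, 0.3 (s = 0.849) | 0.10 | 0 → −0.085 | 0.00 → −0.09 | 5.0% → 5.7% |
| 0, 0, 0.5 (s = 1.414) | 0.10 | 0 → −0.141 | 0.00 → −0.14 | 4.6% → 6.4% |
| 0, 0, 0.5 | 0.20 | 0 → −0.283 | 0.00 → −0.28 | 5.0% → 11.1% |

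In the last three rows there is no true effect, so rejection is type I error. In the third row the adjusted value also misses the direct effect of 0.30, because of the shared cause.

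**Second set of assumptions.** 25 per arm, outcome SD 1, attendance in SD units.
- Mediation only: gap 0.5 SD, 0.4 per SD. Total effect 0.5 × 0.4 = 0.20; adjusted 0.20 − 0.4 × 0.5 = 0.00.
- True null, shared cause with paths of 0.5 each: s = 0.25. Gap 0.5 gives −0.125 (simulated −0.12, type I error 7%). Gap 0.8 gives −0.20 (simulated −0.20, type I error 10%).

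**Dependence on model form.** Two-visit random-intercept model, 400 per arm, 25 runs, inputs as in the third table row:

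| Quantity reported | Without participation | With participation |
|---|---|---|
| Group-by-time, participation as main effect only | 0.54 | 0.54 |
| Adjusted week-8 group difference, main effect only | 0.53 | 0.34 |
| Group-by-time, with participation × time | 0.54 | 0.15 |
| Group difference in change | 0.54 | 0.15 |

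The first row is unchanged because participation takes one value per person and cancels from the week-8 minus baseline contrast. With week-8 data missing for the 20% with lowest attendance, that term moved only from 0.35 to 0.37.

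**The case against.** The strongest defence concerns model form. Section 11.4 makes time a factor and follows up group/time differences, and these outcomes are measured only at baseline and week 8. If change were the response, each person would have one value and neither a time factor nor a mixed model would be needed. The coherent reading is therefore repeated values with change as a contrast. With complete data and participation as a main effect, the group-by-time term is then untouched. This stands, and a reader who infers that the comparison is necessarily biased goes too far. But the section also describes LS-mean change and excludes none of the vulnerable forms.

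Bias also needs an attendance gap. The arms are balanced for sessions and volume (section 7.1) and share the same adherence supports (section 7.1.4), so a gap is possible, not given.

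A reader might also infer that every secondary comparison is affected. That is not so: SEES has its own repeated-measures ANOVA, 12RM a paired test in RT only, and preference a one-way ANOVA. Nor is the covariate useless under every reading, since it moved the estimate trivially in the helpful direction when low attenders were missing.

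The null shifts are no larger than the standard error of a difference at 25 per arm, about √(2/25) = 0.28 SD, and the 0.00 in the mediation-only case follows from assuming no direct effect. Both are fair limits on size.

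Two defences do not stand. Use in earlier research does not make a post-randomisation outcome a baseline covariate. And although participation is also the name of a WHODAS domain, section 11.4 uses the word for attendance.

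**Conclusion.** The inconsistency is established from the text: an analysis labelled intention-to-treat conditions on sessions attended after allocation, which is also a primary feasibility outcome. The protocol specifies no version of this model without it and does not label the adjusted model as a mediation or sensitivity analysis.

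The consequence is conditional. The RT versus AIT comparisons from this model can be biased if attendance differs by arm and the model is fitted on change, includes participation × time, or reports the adjusted week-8 group difference. Otherwise, with complete data, the covariate adds nothing to the group-by-time term. Under the assumed attendance gaps, a true null shifted by −0.09 to −0.28 SD. Type I error was about 6% for the 10-point gaps and 7% to 11% for the larger ones. Effects acting through attendance were partly or wholly removed. None of these sizes, nor their direction, can be derived from the protocol.

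The affected outcomes are secondary in an exploratory trial, and the primary feasibility analysis does not use this model. The point should be fixed, but it does not undermine the trial's main question.

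**What to change.** In section 11.4, delete participation from the mixed-model covariates. Keep only variables fixed before randomisation: age, gender and baseline antipsychotic use, stating that the last is the pre-randomisation value from section 4.4. If the relation between attendance and outcome is of interest, report it as a separate analysis labelled exploratory and non-randomised. Attendance can still inform a missing-data method without entering the treatment-effect model.

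The cost is one word in the protocol and one term in the model code. No additional data are needed and participants are not affected.

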**7.1.5 Randomisation Procedure and blinding**

Participants will be randomised once written consent has been obtained and the baseline assessments have been completed.

Participants will be assigned a unique code that will be sent to an independent biostatistician for randomisation using a computer -generated sequence of numbers. Randomisation to either RT or MIIT condition, will occur in a 1:1 ratio, using block randomisation.

Once randomisation has occurred, participants will be notified of their group allocation by an independent staff member to ensure the research team remains blinded to allocation.

There will be no opportunity to change conditions once randomised, however if participants wish they may withdraw from the study and continue to exercise using the equipment and AEP at each CCU independently from the study. If withdrawal occurs, reasons for doing so will be recorded in the CRF. Following randomisation, participants will be asked whether they are happy with the condition they have been randomised to, and this will be recorded in the CRF.

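### For the secondary outcomes analysed by mixed model, Cohen's d is given only after a detected difference and within each arm, so standardised effects pass a significance filter and none is clearly promised for RT versus AIT

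*Protocol*

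**What the plan says.** Section 11.4 (Statistical Analysis) analyses the secondary outcomes by intention to treat in a linear mixed model with treatment group and time as factors plus covariates. Change from baseline to week 8 is expressed as least squares means, and no significance condition is attached to them.

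The next step depends on a group/time result: "differences were detected, posthoc (Bonferroni) analyses will be carried out separately for the intervention and control group, with Cohen’s d estimate of effect sizes". The same paragraph sets the threshold for detection: "All the statistical tests were two-tailed", and the level is given in the words "with the critical P value for significance set at?<?0.05" (the stray question marks come from the text conversion).

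The last paragraph of 11.4 also uses Cohen's d for the SEES domains, without any requirement of a significant test, and grades it from the bottom of the scale: "An effect size of <0.2 reflects a negligible difference". Values from 0.2 to 0.5 are called small.

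Section 11.2.2 (Secondary endpoints) names the comparison of RT with AIT on mental and physical health outcomes. Section 11.3 (Sample Size and Power) describes the trial's purpose and size: "This study will be conducted as an exploratory RCT with feasibility as the primary outcome"; "we aim to recruit 50 participants assuming approximately 25 participants will be assigned to each intervention arm"; "we anticipate 20% drop outs per exercise condition". It states no power, target effect or standard deviation.

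**The concern.** Two things follow from the conditional sentence.

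- **The filter.** Whether an outcome receives a standardised effect depends on whether its test was significant. In a small trial, estimates that clear the threshold are on average larger than the truth, and those that do not clear it have no d at all. The set of d values in the report would be a selected subset.
- **The contrast.** The d is attached to analyses run separately in each arm. It describes change within RT or within AIT, not the difference between them. No d is clearly promised for the comparison that 11.2.2 sets as the secondary endpoint.

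The protocol handles d for SEES without a filter and gives no reason for treating the mixed-model outcomes differently. This is a rule the protocol states, not a detail left open: an analysis plan that followed it would inherit the filter. In an exploratory trial with no power statement, the secondary estimates and their uncertainty are more informative than which of them passed a test.

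**Working it through.** **Plan's own figure.** There is no power calculation to reproduce. The recruitment arithmetic is consistent: 25 × (1 − 0.20) = 20 completers per arm, and 40 / (1 − 0.20) = 50 in total.

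**Inputs from the protocol.** Two-sided alpha 0.05 (11.4); about 25 per arm and 20% drop-out (11.3); 1:1 allocation (7.1.5). The calculations use 20 and 25 per arm, because an intention-to-treat mixed model lies between completers and all randomised.

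**Assumed inputs, not in the protocol.** The true effects, and the correlation rho between baseline and week 8. Ranges are shown.

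**(a) Between-arm d, simple two-sample comparison.** The smallest significant |d| is t(0.975, 2n − 2) × sqrt(2/n).
- n = 20: 2.024 × sqrt(2/20) = 0.640.
- n = 25: 2.011 × sqrt(2/25) = 0.569.

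Factor = mean |estimated d| given p<0.05, divided by true d (by simulation):

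| True d | Power, n = 20 | Factor, n = 20 | Power, n = 25 | Factor, n = 25 |
|---|---|---|---|---|
| 0.2 | 9.5% | 4.00 | 10.6% | 3.56 |
| 0.3 | 15.2% | 2.73 | 18.0% | 2.44 |
| 0.4 | 23.4% | 2.11 | 28.4% | 1.89 |
| 0.5 | 33.8% | 1.74 | 41.0% | 1.57 |

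**(b) Between-arm difference in change, effect in raw SD units.** This is closer to the planned model. The SD of change is sqrt(2(1 − rho)) raw SDs, so with n = 20 the threshold is 0.640 × sqrt(2(1 − rho)).

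| rho | Threshold, n = 20 | Factor at true d 0.2 (n = 20; 25) | Factor at true d 0.3 (n = 20; 25) |
|---|---|---|---|
| 0.5 | 0.64 | 3.76; 3.41 | 2.59; 2.35 |
| 0.7 | 0.50 | 2.97; 2.69 | 2.07; 1.88 |
| 0.8 | 0.40 | 2.47; 2.24 | 1.74; 1.59 |
| 0.9 | 0.29 | 1.82; 1.67 | 1.34; 1.24 |

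The range is therefore about 1.2 to 3.8.

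**(c) Within-arm change in RT, as the sentence literally describes.** True RT change 0.2 to 0.3, AIT change 0.1 to 0.2, rho 0.5 to 0.8; here the factor is the mean signed change given selection, divided by the true change. If the trigger is the group-by-time interaction, the factor is about 1.0 to 1.9. It is about 1.0 when both arms truly change equally. If the trigger is the time effect, it is about 1.2 to 2.2.

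**(d) With d reported for every outcome.** The selection disappears and the ratio is about 1, apart from the usual small-sample bias of d of about 2%.

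**The case against.** The strongest reply is that the filter is narrow. Least squares mean changes are calculated for the secondary outcomes without any condition, and the SEES d is unconditional. Feasibility is the primary outcome, and nothing in the protocol says the secondary effect sizes will be used to plan a larger trial. All of this stands and limits the point to the standardised effect for the mixed-model secondary outcomes. It does not remove the point, because least squares means are on each instrument's own scale and the text promises neither an interval nor a standardised value for outcomes that miss significance.

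A second reply concerns size. A reader might infer from part (a) that the trial's effect sizes are in general inflated two- to four-fold. The documents do not support that. The factor is for a between-arm two-sample d under assumed true effects, whereas the quoted sentence attaches d to analyses in each arm, and its trigger may include a time effect.

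A reader might also infer that no small between-arm effect could ever be reported, since 0.64 lies above the small band. That fails as a certainty. On change scores the threshold falls to about 0.50, 0.40 and 0.29 raw SDs at correlations of 0.7, 0.8 and 0.9, and the protocol gives no correlation. The band itself stands in the SEES paragraph.

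Finally, how d is tabulated and labelled could be left to an analysis plan. That is true of layout. It is not true of a condition the protocol already fixes.

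**Conclusion.** The point holds for the mixed-model secondary outcomes. Section 11.4 makes Cohen's d conditional on a detected difference and places it within arms, so standardised effects are selected on significance and the RT-AIT contrast is left without a clearly promised d.

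No single inflation factor can be stated, because all three ranges rest on assumed true effects and, for change scores and within-arm change, on an assumed correlation. The between-arm factors apply if d is read as a comparison of arms; the smaller within-arm range applies to the sentence as written. What does not depend on these assumptions is the omission: any outcome without a detected difference gets no d.

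The primary feasibility outcome is untouched. This is a correction that should be made, at low cost, and not a threat to the trial's main conclusion.

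**What to change.** In 11.4, remove the condition of a detected group/time difference as far as effect sizes are concerned, and state: for every secondary outcome analysed by the mixed model, the RT-AIT difference in change from baseline at week 8, its 95% CI, and Cohen's d with 95% CI will be reported whatever the p value. Within-arm results may be shown in addition, but not in place of that contrast. The choice of standard deviation for d can be left to the analysis plan, if it is fixed before the data are seen.

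The intervals will be wide: for a simple two-sample d with 20 per arm the half-width is about 1.96 × sqrt(2/20) = 0.62, which is why d should be shown with its interval.

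The cost is one sentence and a longer results table. No new data, visits or participants are needed.
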